### 2.2 Secondary target variables

Secondary outcome measures are used to identify the most common barriers for students to make infrequent or no use of health-related services, measured using a five-point scale (from "very important" to "not important").

Moreover, the use of existing offerings and their level of awareness will be asked in a four-step response format (used so far; known but not used; not known but interested; not known and not interested).

In a final step, group-specific barriers to the use of existing services as well as their awareness will be identified. These secondary outcome variables are additionally examined for gender and faculty differences.

## 3. Study population

### 3.1 Inclusion and exclusion criteria

Only students from the 11 faculties of the ALU Freiburg are allowed to participate in the needs analysis. For this purpose, the following inclusion and exclusion criteria have been defined:

Inclusion criteria:

Enrolled at the ALU Freiburg≥18 years of age

Exclusion criteria:

Institutes or universities that do not belong to ALU Freiburg (private institutes, university of education, universities of other sponsors in Freiburg, etc.).Employees of the ALUDoctoral studentsStudents with physical impairments that prevent them from moderate and/or strenuous physical activity.Students with an impairment/illness that strongly influences their dietary behaviorStudents who have a severe psychological impairment

### 3.2 Number of participants in the studies

According to recent student statistics at ALU Freiburg, 24,391 students from over 100 nations are enrolled in 180 study programs at 11 faculties. Of these, 12,908 are female students and 11,483 are male students. The goal is to have > 2% of the students in each faculty participate in the survey to ensure a representative sample of the faculties. Thus, in total > 500 university students should be surveyed [37].

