## 5. Biometry

The present study is an exploratory study conducted monocentrically and prospectively at ALU Freiburg in Germany. Based on the 2014 German Student Survey on sample selection and representativeness of data, a sample of > 500 students is recommended to obtain a sufficiently large number of students in the different subject distributions [37]. Approximately 0.9% of all students at the universities took part in a survey in the winter semester 2012/13. Participation varied between the universities by 0.6–1.6%. It was pointed out that for representative statements, it is not so much the relative proportion of the sample to the population that is important, but the absolute size of the sample. With this in mind, > 500 students are expected to participate in the survey in the present investigation, thus creating a representative sample.

Data analysis will be conducted using IBM SPSS Statistics version 26.0. All tests are two-sided and the significance level will be set at α = 5%. Effect size d will be calculated according to Cohen (1988) and interpreted as follows: < 0.2 (no effect); ≥ 0.2 (small effect); ≥ 0.5 (moderate effect); and ≥ 0.8 (large effect) [65]. To test the data for normal distribution, if necessary, the Shapiro-Wilk test will be chosen due to the large sample size.

In principle, the data collected on prevalence in relation to exercise, nutrition, relaxation and stress reduction, self-management, psychosocial health, and sociodemographic data of students of the ALU Freiburg will be illustrated and presented by means of descriptive statistics and graphs, since this is primarily a description of the opportunity sample. Therefore, the number of the sample population is given as N and as a percentage. For interval-scaled data, the mean (MW) and ± standard deviation (SD) will also reported. Along with the MW and SD, the median will also be given for the descriptive analysis of the parameters.

In order to investigate whether the national and international guidelines are met by students in the respective areas, a Chi-square test will be performed by a cross-tabulation. At the same time, the cross-tabulations will also be used to compare the respective faculties. Using a t-test for independent samples, differences in characteristic expressions, such as gender and faculty differences, will be analyzed. If there is no normal distribution, the Mann-Whitney U-test will be applied.

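### Neither >2% per faculty nor a total of >500 makes the sample representative, and >500 is necessary but not sufficient for the per-faculty goal

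*Protocol article*

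**What the plan says.** Section 3.2 of the protocol article gives the base as "24,391 students from over 100 nations are enrolled in 180 study programs at 11 faculties". It aims to see "> 2% of the students in each faculty participate in the survey to ensure a representative sample of the faculties", and it continues: "Thus, in total > 500 university students should be surveyed".

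Section 5 (Biometry) reaches the same total by another route. Citing the 2014 German Student Survey, it says that "a sample of > 500 students is recommended to obtain a sufficiently large number of students in the different subject distributions". It then reports that "Approximately 0.9% of all students at the universities took part in a survey in the winter semester 2012/13", with a range across universities of 0.6% to 1.6%. On what makes a sample representative, it remarks: "it is not so much the relative proportion of the sample to the population that is important, but the absolute size of the sample". It concludes that "> 500 students are expected to participate in the survey in the present investigation, thus creating a representative sample".

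Later in section 5 the analysis is described as primarily the description of an opportunity sample. Section 3.3 recruits through an open link on the learning platform, social platforms and a kick-off event. It mentions no faculty quota or stratification.

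**The concern.** Three things do not fit together.

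- The per-faculty goal is set as a percentage and is said to secure representativeness. Section 5 says that percentage is the less important quantity.
- The total leaves almost no room above 2% overall, although the goal applies to each of 11 faculties separately.
- Both sections claim representativeness for a self-selected sample that section 5 itself calls an opportunity sample.

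This matters because the faculty results carry weight. Section 2.1 examines every primary target variable for gender and faculty differences to find target groups, section 2.2 does the same for the secondary variables, and section 7 wants tailored programmes for different student groups. A reader who accepts the representativeness statements will trust faculty prevalences that rest on a few dozen volunteers each.

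**Working it through.** **Inputs.** From section 3.2: N = 24,391 students, 11 faculties, goal >2% per faculty, total >500. From section 5: participation in the earlier survey 0.9% (0.6–1.6%). Faculty sizes are not given, so per-faculty figures use an average faculty or an assumed layout.

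**1. The plan's own total.** 0.02 × 24,391 = 487.8, so 488. The stated >500 is consistent with this. The multiplication is sound.

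**2. Room above 2%.** 500 / 24,391 = 2.05%, and 500 − 488 = 12 respondents to spare across 11 faculties. If counts could be steered exactly, 495 to 498 respondents would put every faculty above 2% (range over an equal and an uneven assumed layout). Section 3.3 describes no such steering.

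**3. Without quotas (illustrative).** Take 11 equal faculties of 24,391 / 11 ≈ 2,217. Since 0.02 × 2,217 = 44.3, each needs at least 45 respondents. With equal propensity to respond and a total of 501, the expected count is 501 / 11 = 45.5 per faculty. The chance that a given faculty reaches 45 is then about 0.56 (binomial, 501 trials, probability 1/11), so about 11 × 0.56 ≈ 6 of 11 faculties meet the goal on average and about 5 fall short. The simulated chance that all 11 exceed 2%, for equal and uneven assumed faculty sizes (600 to 4,691), is:

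| Total | Chance that all 11 exceed 2% |
|---|---|
| 501 | about 0 |
| 600 | 21–39% |
| 700 | 72–96% |
| 800 | 93–99.9% |

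Unequal uptake between faculties would generally make the goal harder to reach.

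**4. What 2% of a faculty gives.** Nominal 95% half-width = 1.96 × √(p(1 − p)/n), as if respondents were a simple random sample:

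| n | p = 0.3 | p = 0.5 (worst case) |
|---|---|---|
| 20 (2% of a faculty of 1,000) | 20.1 points | 21.9 points |
| 40 | 14.2 points | 15.5 points |
| 45 (average faculty) | 13.4 points | 14.6 points |
| 500 (whole university) | 4.0 points | 4.4 points |

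The finite-population correction at a 2% fraction multiplies these by √0.98 ≈ 0.99, so it changes almost nothing. Precision is set by n, as section 5 says, and the 2% rule lets n shrink with the faculty.

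**5. Expected uptake.** The 2.05% needed for 500 is 2.05 / 0.9 ≈ 2.3 times the cited mean and 2.05 / 1.6 ≈ 1.3 times the cited maximum. Section 5 moves from these rates to an expectation of >500 and gives no reason for the difference.

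**6. Representativeness.** Section 3.2 makes it follow from a share per faculty. Section 5 makes it follow from a total and ranks absolute size above share. The same section calls the data an opportunity sample, for which neither a share nor a total removes self-selection.

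**The case against.** The strongest reply is that section 3.2 argues from the faculty goal to the total and not the reverse. On that reading >500 is an open lower bound that follows correctly from 2% of enrolment, no stop at 500 is stated, and the per-faculty goal stands as its own stricter target. This is right: a reader might infer an arithmetic error or a promise that 500 guarantees every faculty, and the text contains neither. The figures at 501 describe only the edge of what the plan accepts, under assumed faculty sizes.

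A reader might also apply 0.6–1.6% to 24,391, obtain 146 to 390 respondents, and conclude that the target will be missed. The document does not support that. The rates come from another survey in 2012/13, they lead into the remark on absolute size, and they read as precedent for a small sampling fraction. Recruitment here may do better. What stands is narrower: the rates sit directly before an expectation that exceeds all of them, and no reason is given.

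Finally, the study is exploratory and mainly descriptive, and it claims no power for faculty comparisons. Low power between two faculties of 45 would therefore contradict no stated figure. Section 5 also weighs absolute size against proportion and does not rule proportion out, so a recruitment goal aimed at spread across faculties can coexist with it. None of this rescues the statements that 2% per faculty, or >500 in total, yields a representative sample.

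**Conclusion.** The concern holds as a correction of stated claims. The representativeness statements in sections 3.2 and 5 attribute to the sample a property that the design does not give it, and section 5's own remarks on absolute size and on the opportunity sample conflict with them. A total of >500 is necessary but not sufficient for >2% in all 11 faculties. Close to that minimum, about 5 of 11 would be expected to fall short even with equal uptake (equal faculty sizes assumed). Meeting the goal exactly leaves about 45 students in an average faculty, with a half-width of about 13 points at 30% prevalence and about 15 at worst, before any self-selection bias.

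The expected 2.05% uptake lacks a stated reason, but it is not shown to be unattainable. The overall total of >500 need not change.

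**What to change.** In sections 3.2 and 5 of the protocol article:

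1. Delete the statements that 2% per faculty, or >500 in total, gives a representative sample.
2. Describe >500 as the overall minimum, and the per-faculty goal as a separate target checked against the actual counts. Faculty affiliation is already collected (section 4.2.6).
3. Replace the 2% criterion with an absolute minimum number of respondents for reporting a faculty separately, for example about 40 (half-width 15.5 points at worst). The exact number is a choice for the investigators. Report smaller faculties only descriptively or pooled.
4. State nominal precision, about 4.4 points at n = 500 in the worst case, with the caveat that it covers sampling error only and not self-selection.
5. Either justify the expected uptake of 2.05% or stop presenting the cited participation rates as support for it.

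The cost is a few rewritten sentences and no extra participants. The downside is that faculty-level statements become less favourable and some small faculties will not be reported separately, which limits the search for faculty target groups in section 2.1.

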### 3.3 Recruitment measures

To ensure that all university students are actually informed about the survey and can potentially be recruited to participate in the needs assessment, a link to the survey will be provided via the University of Freiburg’s central learning platform ILIAS. Students can use this link to obtain both information and access to the survey. Further recruitment activities are to take place via the social platforms of the Student Health Management (SGM). Likewise, the SGM kick-off will be used to advertise participation in the needs assessment. In addition to the application, direct participation via provided PC access will be made possible.

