## 4. Methodology and implementation

### 4.1 Informing and obtaining the consent of the students

Before answering the questionnaire, students will be informed about the scope of the survey. For that purpose, a participant information sheet is provided on the website of the survey. In layman’s terms, this contains the background, the objective and the content framework of the survey. Moreover, the participant information sheet lists and describes detailed information on data management and data protection. As the survey is completely anonymous on a website and there is no prior contact with the examiners, participation in the survey is based on the assumption that the students have given their informed consent. The login process via the University of Freiburg ensures that no minors participate in the surveys.

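### Part of the recruitment runs through the student health service's own channels and no entry route is recorded, so awareness of existing services may be overestimated by an amount that cannot be measured

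*Protocol article*

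**What the plan says.** Protocol article, section 3.3, names the ways into the survey. The first is general: "a link to the survey will be provided via the University of Freiburg’s central learning platform ILIAS", so that every student can be informed. Further recruitment then uses the SGM's social platforms and its launch event: "Likewise, the SGM kick-off will be used to advertise participation in the needs assessment". Finally, "In addition to the application, direct participation via provided PC access will be made possible"; the article does not say where these computers stand.

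Section 2.2 makes awareness and use a secondary outcome: "the use of existing offerings and their level of awareness will be asked in a four-step response format". The answers run from used, through known but unused, to two grades of not known. Section 2 sets the scope as services that already exist, inside the university or outside it. Section 2.2 adds that the secondary outcomes are examined by gender and faculty.

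The abstract and section 7 present the SGM as the vehicle for the health measures. The abstract also says that the two-yearly surveys serve to check the effect of those measures. Entry route is not among the characteristics listed in section 4.2.6, and section 5 contains no analysis by route. Section 5 calls the data a sample of opportunity, but also claims representativeness because more than 500 students are expected.

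**The concern.** The outcome asks whether a student knows a service, and some students are invited by the organisation that offers services. Two mechanisms push the same way. People who follow the SGM's platforms or attend its launch are likely to know more already (selection). The launch may also inform them shortly before they answer (exposure). Gender and faculty capture neither mechanism, and a larger sample does not reduce the bias.

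Two uses of the result are at stake. Section 2 derives the need for interventions from the primary and secondary goals, so overstated awareness can hide a need. The repeat surveys are meant to show whether measures work, so a change in the mix of routes from one round to the next can look like a change in awareness. Because the survey is anonymous, a route that is not stored at entry cannot be recovered afterwards by an analysis plan.

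**Working it through.** **The plan's own figure.** Section 3.2 gives 24,391 students (12,908 + 11,483 = 24,391) and a target above 2%. 0.02 × 24,391 = 487.8, consistent with the stated minimum of just over 500 (500 / 24,391 = 2.05%). There is no power calculation to reproduce. I use n = 500 below.

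**Formula.** Let s be the share of respondents entering through SGM channels, p the awareness among other entrants (taken as the population value) and pS the awareness among SGM entrants. Then:

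- observed awareness = (1 − s) × p + s × pS
- bias = s × (pS − p)
- 95% half-width = 1.96 × √(p(1 − p)/n)
- share at which the bias equals the half-width: s* = half-width / (pS − p)

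**Inputs.** The documents give none of s, p or pS. Assumed ranges: p = 20% or 30%; pS = 60%, 90% or 100%; s = 10%, 25% or 50%.

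**Half-widths at n = 500.** p = 20%: 1.96 × √(0.2 × 0.8/500) = 3.5 points. p = 30%: 1.96 × √(0.3 × 0.7/500) = 4.0 points.

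**Bias in percentage points, and threshold share.**

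| p | pS | s = 10% | s = 25% | s = 50% | s* |
|---|---|---|---|---|---|
| 20% | 60% | +4.0 | +10.0 | +20.0 | 8.8% |
| 20% | 90% | +7.0 | +17.5 | +35.0 | 5.0% |
| 20% | 100% | +8.0 | +20.0 | +40.0 | 4.4% |
| 30% | 60% | +3.0 | +7.5 | +15.0 | 13.4% |
| 30% | 90% | +6.0 | +15.0 | +30.0 | 6.7% |
| 30% | 100% | +7.0 | +17.5 | +35.0 | 5.7% |

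The threshold runs from 4.4% to 13.4% of respondents, that is 22 to 67 of 500 (0.044 × 500; 0.134 × 500). If s is near 0, or pS is near p because the SGM does not promote the service, the bias is near 0.

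**Between rounds.** With p and pS unchanged, a change in route mix moves observed awareness by (s2 − s1) × (pS − p). Example with p = 20%, pS = 60% and s falling from 25% to 10%: observed awareness goes from 30% to 24%, a drop of 6 points with no true change. For two independent rounds of 500, the 95% half-width of the difference is 1.96 × √(0.30 × 0.70/500 + 0.24 × 0.76/500) = 5.5 points, so this artefact alone would lie outside it.

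**The case against.** The ILIAS link comes first and is aimed at everyone; the SGM routes are additional. A reader might infer that awareness is measured only or mainly in students reached by the SGM. Section 3.3 does not support that.

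The outcome covers services already in place, including external ones, while the SGM is new. The article says that the launch advertises the survey, not that it advertises those services. Past use is also unlikely to be created by a launch event. This stands: the risk is greatest for awareness of SGM-linked offers and weaker elsewhere, although over-recruiting SGM followers could still raise reported use.

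The formula cannot separate exposure from selection. Students who already follow the SGM belong to the population. If they form a share π of all students, the over-sampling bias is (s − π) × (pS − p), so the table applies where π is small. This stands as a limit on the figures.

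A reader might also see a contradiction between the offer that "direct participation via provided PC access will be made possible" and the statement in section 4.1 that "the survey is completely anonymous on a website and there is no prior contact with the examiners". The text does not show one: a provided computer can open the same anonymous website, and no examiner is said to be present. Under-reporting of sensitive answers on those computers is conjecture, as is any difference between faculties in route.

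Finally, a condensed article may leave link set-up to the full protocol. That is possible. But the recruitment channels and the gender and faculty breakdown are stated choices, and together they leave the problem open unless route is captured at entry.

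**Conclusion.** The point holds as a risk, not as a demonstrated distortion. Part of the recruitment uses channels of the organisation whose offers fall within the outcome, and the article gives no means of seeing whether that matters. Awareness of existing services, especially SGM-linked ones, may be overestimated. On the assumed values, the bias passes the sampling error of 3.5 to 4.0 points once roughly 4-13% of respondents enter through the SGM, and it may equally be close to zero. To say that the outcome is altered by recruitment would go beyond the documents, since they give neither the share per route nor the difference in awareness. For an exploratory, descriptive secondary outcome this is an inexpensive improvement that bears on both the needs assessment and the comparison of rounds. The primary outcomes and the sample size are not affected by this point.

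**What to change.** In section 3.3, give each route (ILIAS, SGM social platforms, kick-off or provided computer) its own anonymous survey link, and keep these links in every round, so that route is stored without personal data. In sections 2.2 and 5, state that awareness and use will be reported by route, and add a pre-stated sensitivity analysis limited to ILIAS entries. When rounds are compared, show the route mix of each.

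State the limit as well: the entry link is an imperfect marker of exposure, because an SGM follower or launch attendee can still enter through ILIAS. For the same reason ILIAS entries should be the sensitivity analysis and not replace the main estimate; restricting to them also drops students who are genuinely aware and could bias awareness downward. The cost is a little set-up per round and one extra stratified table. Anonymity and sample size are unchanged.

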## 4. Methodology and implementation

### 4.1 Informing and obtaining the consent of the students

Before answering the questionnaire, students will be informed about the scope of the survey. For that purpose, a participant information sheet is provided on the website of the survey. In layman’s terms, this contains the background, the objective and the content framework of the survey. Moreover, the participant information sheet lists and describes detailed information on data management and data protection. As the survey is completely anonymous on a website and there is no prior contact with the examiners, participation in the survey is based on the assumption that the students have given their informed consent. The login process via the University of Freiburg ensures that no minors participate in the surveys.

### 4.2 Questionnaire survey

At the start of the study and subsequently at two-year intervals until 2026, situation and needs analyses will be conducted using validated and evaluated questionnaires. Data will be collected via an anonymous and self-administered online questionnaire via Social Science Survey [SoSci Survey] [38]. All questionnaires applied have been validated and have already been employed in various studies addressing comparable issues. No modifications have been made to the questionnaires in the context of the present investigations that would necessitate a re-validation.

#### 4.2.1 Physical activity

Physical activity will be assessed with the International Physical Activity Questionnaire (IPAQ) [39]. In addition, following Wallace et al. (2000), the weekly sitting time (WST) for studying, at the computer and for screen-related work will be queried via three items [40]. Based on Kramer and Fuchs (2010), possible barriers and barrier management in the process of sports participation will be identified via 13 items [41].

